### Statistical analysis

The primary outcome measure is the composite prevalence of CT, NG, TV, syphilis and hepatitis B in this population.

Other outcome measures include:

Individual prevalence of each STI (CT, NG, TV, syphilis, hepatitis B and HIV).Uptake of testing.Uptake of treatment.Uptake of partner notification.STI yield (number of participants with a positive STI result/total number of eligible individuals).Prevalence of AMR to ceftriaxone, cefixime, azithromycin and ciprofloxacin in NG isolates.Prevalence of preterm birth, miscarriage and low birth weight.

Categorical variables will be described using frequencies and percentages. Continuous variables will be described using either mean (SD) or median (IQR) for normally distributed and non-normally distributed data, respectively. Multivariable logistic regression will be used to assess factors associated with presence of STIs. Clustering will be adjusted for at clinic level. Logistic regression will also be used to assess the relationship between STI diagnosis and birth outcomes.

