A client-referral approach will be used for notification of sexual partners. Women will be counselled on the importance of their partners receiving treatment and given partner notification (PN) slips for their partners to return for presumptive treatment. Although partners will be able to attend any clinic, treatment will be provided free of charge if they return to the study clinic.

Women newly diagnosed with HIV will be referred for antiretroviral therapy as per local PHC processes. Women newly diagnosed with hepatitis B will have hepatitis B viral load and alanine aminotransferase testing, alongside referral to a gastroenterology specialist in secondary care. Although hepatitis B vaccination is currently included in the Zimbabwe national vaccination schedule at 6, 10 and 14 weeks, birth dose vaccination is not yet standard of care in Zimbabwe. Birth dose vaccines will therefore be provided by the IPSAZ Study. This is likely to be logistically complex and bespoke strategies for implementation will be designed in conjunction with healthcare teams at the individual PHCs and with local secondary care providers.

Birth outcome data will be collected from birth registers, including birth weight, gestation, mode of delivery and stillbirth. Estimated due date, which will be compared with actual birth date to determine prematurity, will be based on last menstrual period. Participants will also be contacted by telephone post partum to facilitate this process by providing information on date and location of birth, and to provide supplemental data if necessary if the birth register is incomplete. Participants will also be asked about number of ANC visits, and for women with positive STI results, if they gave the PN slip to their partner, and if their partners were treated.

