### Sample size calculations

There are limited data on STI prevalence in pregnant women in Zimbabwe. A prevalence of curable STIs between 32.0% and 37.0% has been reported in South Africa and Zambia.^12–16^ Our recent studies among female youth in Harare have demonstrated combined CT/NG prevalence between 18.2% and 19.5%.^18 19^ The prevalence of hepatitis B in pregnant women in South Africa has ranged between 3.1% and 5.3%.^20–22^ Therefore, a conservative estimate of composite prevalence of curable STIs and hepatitis B is 30.0%. With a desired precision of 3% and alpha of 0.05, a sample size of 896 is required. To allow for invalid test results, 1000 pregnant women will be screened. The minimum detectable ORs for factors associated with the presence of STIs at different composite prevalence of STIs are shown in table 3.

**Table 3 T3:** Minimum detectable ORs for factors associated with presence of STIs

Sample size*	STI prevalence	Precision	Smallest OR detected at 80% power	Smallest OR detected at 90% power
896	20%	2.6%	1.74	1.89
	25%	2.8%	1.67	1.80
	30%	3.0%	1.63	1.75

*Assuming a prevalence of a risk factor of 20% among those without STIs.

STIs, sexually transmitted infections.

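### Birth weight is collected, but the only model named for its association with STI diagnosis is logistic regression; adding a linear model of birth weight alongside would recover precision at almost no cost

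*Protocol article*

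**What the plan says.** Under Study procedures, the protocol article states: "Birth outcome data will be collected from birth registers, including birth weight, gestation, mode of delivery and stillbirth". The postpartum telephone call fills gaps in the registers.

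Under Statistical analysis, the birth entry in the list of other outcome measures is: "Prevalence of preterm birth, miscarriage and low birth weight". All three are binary. The same section then gives the method for the association: "Logistic regression will also be used to assess the relationship between STI diagnosis and birth outcomes". No other model is named for it.

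The Economic evaluation section uses miscarriage, stillbirth, low birth weight and prematurity as endpoints of the decision tree. The Discussion says there is no formal comparison of birth outcomes between women who did and did not receive the intervention. No power, effect size or expected rate is given for the association between STI diagnosis and birth outcomes.

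**The concern.** Birth weight reaches the study as a measured quantity. Logistic regression can use it only after it has been reduced to low birth weight, yes or no. That step discards the differences among babies on the same side of the cut-off, and when the outcome is uncommon most of the information goes with it.

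Nothing in the article requires this association to be examined only on the cut. The prevalence of low birth weight is needed for reporting and to support the economic model, but a model of mean birth weight can stand beside it.

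At stake is how informative this secondary result will be. With 1000 women screened, a modest real difference in birth weight could produce a wide odds ratio whose interval includes 1, which could be misread as no association.

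**Working it through.** **The plan's own figure.** The sample size is set for the composite prevalence: "With a desired precision of 3% and alpha of 0.05, a sample size of 896 is required". With n = z²p(1−p)/d², p = 0.30, d = 0.03 and z = 1.96, n = 896.3, which matches. The precisions in Table 3 (2.6%, 2.8%, 3.0%) follow from 896 women. The odds ratios in that table also reproduce, if a continuity correction is used. They concern factors associated with having an STI, so they say nothing about power for birth outcomes.

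**Inputs from the document.** 1000 women screened; composite prevalence 30%, taken here as the share exposed; alpha 0.05, taken as two-sided.

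**Inputs assumed, because the document does not give them.** 800 births with data, so n₁ = 240 exposed and n₀ = 560 unexposed; low birth weight p₀ of 8% to 15% in STI-negative women; birth weight normal, with STI shifting it down by d standard deviations; clustering by clinic and covariates ignored.

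**Formulas.**
- Low birth weight rate in exposed women: p₁ = Φ(Φ⁻¹(p₀) + d).
- Logistic: z = ln(OR)/SE, with SE = √[1/(n₁p₁(1−p₁)) + 1/(n₀p₀(1−p₀))].
- Linear: z = d/√(1/n₁ + 1/n₀).
- Power = Φ(z − 1.96).

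**One case in full: p₀ = 10%, d = 0.20.**
- p₁ = Φ(−1.282 + 0.20) = 14.0%; OR = 1.46; ln(OR) = 0.380.
- SE = 0.234; z = 1.63; power 37%. The expected odds ratio of 1.46 carries an approximate 95% CI of 0.93 to 2.31.
- Linear: √(1/240 + 1/560) = 0.0772; z = 0.20/0.0772 = 2.59; power 74%.

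**Across the assumed range.**

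| Shift (SD) | Logistic on the cut, p₀ 8–15% | Linear |
|---|---|---|
| 0.15 | 20–26% | 49% |
| 0.20 | 34–43% | 74% |
| 0.25 | 50–62% | 90% |
| 0.40 | 90–96% | >99% |

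With 20% exposed and 700 births, a 0.20 SD shift gives 25–32% against 56%.

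**Information kept by the cut.** For a small normal shift this is φ(z_q)²/[q(1−q)], where q is the low birth weight rate and z_q its normal quantile. It is 30% at q = 8%, 34% at 10% and 43% at 15%.

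**A case that goes the other way.** Suppose only 10% of exposed women are affected, each by 2 SD, with p₀ = 10%. By simulation, power is then about 73% on the cut and 64% for a comparison of means.

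**The case against.** The strongest case against has four parts.

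- **The method fits the declared outcomes.** Preterm birth, miscarriage and low birth weight are binary and clinically meaningful, and they are also endpoints in the economic model. Logistic regression is the matching model. This stands: a reader might infer that the plan uses a wrong method, and the documents do not support that.
- **The article does not say that no other model will be fitted.** It is condensed, and a fuller protocol or analysis plan may include a linear model. This stands as a limit: one can say only that logistic regression is the one model named. It does not remove the point, because the article states a method for this association and that method can be commented on.
- **The size of the loss is assumed.** A reader might conclude that about half the power is lost. That ratio holds only for some combinations of small shift and low birth weight rate, and none of these inputs is in the documents. At 0.4 SD little is lost, and in the subgroup case the cut does better. This stands in full.
- **Mean birth weight is not a listed outcome.** Making it the main analysis would change the question being asked. This also stands, and it is why the linear model belongs beside the logistic one and not in its place.

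Extending the point to gestation or preterm birth is tempting too. The article describes comparing the birth date with a due date based on last menstrual period in order to determine prematurity, and no gain has been worked out for that outcome. Miscarriage and stillbirth are binary by nature.

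**Conclusion.** The point holds for birth weight, as a minor matter of efficiency. No stated figure is wrong and no stated analysis needs to be withdrawn.

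Under the assumptions listed, the gap for a 0.20 SD shift is roughly 30 to 40 percentage points of power in favour of the linear model. It is 10 points or less at 0.4 SD and may reverse if harm is concentrated in a few women. Nothing in the documents shows which pattern is more plausible. Women who test positive are to be treated, so the size and shape of any remaining association are unknown. That uncertainty favours reporting both analyses.

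**What to change.** In Statistical analysis, keep the logistic regressions for low birth weight, preterm birth and miscarriage as planned, and add one sentence, for example: *Alongside these, birth weight in grams will be regressed on STI diagnosis by linear regression, adjusted for clinic, and the mean difference reported with its 95% confidence interval.* The listed prevalences and the inputs to the economic model stay as they are.

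The cost is one sentence and one extra regression on data already being collected. The downsides are small: one more secondary result to report, a mean difference that is less directly clinical than low birth weight, and possible rounding of weights in the registers.

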**Methods and analysis:**

A prospective interventional study will be conducted in ANC clinics in Harare province, Zimbabwe. One thousand pregnant women will be recruited when registering for routine ANC. Alongside routine HIV and syphilis testing, participants will be offered an integrated screening package including testing for *Chlamydia trachomatis* (CT), *Neisseria gonorrhoeae* (NG), *Trichomonas vaginalis* (TV) and hepatitis B. All individuals with STIs will receive treatment, partner notification services, risk reduction counselling and referral if needed according to national guidelines. Gonorrhoea samples will be cultured and tested for antimicrobial resistance as per WHO enhanced gonococcal antimicrobial surveillance programme guidelines.

The primary outcome measure is the composite prevalence of CT, NG, TV, syphilis and hepatitis B. A mixed-methods process evaluation and economic evaluation will be conducted to understand the acceptability, feasibility and cost-effectiveness of integrated STI testing, compared with standard of care (syndromic management).

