### Study procedures

The full schedule of events for pregnant women is described in table 1. Following consent, an interviewer-administered questionnaire will collect sociodemographic data, clinical history including STI symptoms and recent antibiotic use, sexual and obstetric history. Contact information will be collected for follow-up.

**Table 1 T1:** Schedule of events for pregnant women

Participants	Activity	Day 0 (study entry)	Days 1–5	Days 4–14	On partner attendance	Birth	Post partum (planned telephone follow-up)
All	Informed consent	X					
All	Questionnaire	X					
All	HIV testing	X					
All	Syphilis testing	X					
All	HBV testing	X					
All	Vaginal swab collection	X					
All	CT/NG testing	X					
All	TV testing	X					
STI test positive	Health education	X					
HBV test positive	Venepuncture	X					
HBV test positive	HBV viral load and ALT testing	X					
HBV test positive	Referral to secondary care	X					
HIV test positive	Referral as per PHC processes	X					
CT/NG/TV/syphilis test positive	Provision of treatment	X					
CT/NG/TV/syphilis test positive	Partner notification advice and slip	X					
NG test positive	Cervical swab collection	X					
NG test positive	Plating of cervical swab and incubation at laboratory	X					
STI test positive Not treated on day 0	Contact participant by telephone and ask to return to PHC for treatment		X				
Cultured NG isolate	Storage of isolate at −80°C			X			
Partners	Provision of treatment to partners who attend PHC				X		
HBV test positive	Provision of HBV birth dose vaccine coordinated with PHC and secondary care					X	
CT/NG/TV/syphilis test positive	Contact by telephone to collect data on partner notification process						X
All	Contact by telephone to collect birth outcome data						X
All	Review of birth registry records to supplement birth outcome data from participants						X

ALT, alanine aminotransferase; CT, *Chlamydia trachomatis*; HBV, hepatitis B virus; NG, *Neisseria gonorrhoeae*; PHC, primary healthcare clinic; STI, sexually transmitted infection; TV, *Trichomonas vaginalis*.

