Participants will provide three self-taken or provider-taken vaginal swab samples. One vaginal swab sample will be tested for CT and NG using the Xpert CT/NG assay (Cepheid), which has an analytical time of 90 min. The GeneXpert device will be operated using a rechargeable powerpack to provide an uninterrupted power supply. The second swab will be tested for TV using the OSOM Trichomonas Rapid Test (Sekisui Diagnostics), which has an analytical time of 10 min.^30^ The third swab will be stored for future studies including possible whole-genome sequencing. A fingerprick blood sample will be taken for HIV, syphilis and hepatitis B testing using the SD BIOLINE HIV/Syphilis Duo (Abbott Diagnostics Medical Co) (analytical time 20 min) and HBsAg 2 (Abbott Diagnostics Medical Co) (analytical time 30 min) rapid tests, respectively.^31^ HIV and syphilis testing, referral to HIV services, syphilis treatment and partner notification for those with HIV or syphilis are already part of routine care. The study team will work with health facility staff to integrate the additional STI testing with routine ANC services to prevent duplication of procedures.

Participants with positive test results and their partners will be managed in line with Zimbabwe national treatment guidelines.^32^ For participants with an STI syndrome on presentation, immediate treatment will be provided for syndromes such as pelvic inflammatory disease and genital ulcer disease, where testing will not alter management. For vaginal discharge syndrome, participants will ideally wait for their results to receive tailored treatment; however, they will receive metronidazole regardless of results, in order to cover for bacterial vaginosis. For symptomatic participants not willing or able to wait or return for their results, they will have the option to receive full syndromic treatment.

Participants will ideally collect their results and receive treatment if necessary within the same clinical visit. Participants who test positive for an STI but are unable to receive same-day treatment will be actively followed up by telephone, up to five times over a 28-day period, to advise them to return for treatment.

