### Economic evaluation

Cost-effectiveness will be evaluated as the ratio of incremental costs and incremental effects of POC testing for CT, NG and TV, in comparison with routine care using syndromic management. Total costs and effects will be estimated for each arm, with incremental values calculated from these estimates.

Clinical endpoints include mild infection, pelvic inflammatory disease, infertility and adverse birth outcomes including miscarriage, stillbirth, low birth weight and prematurity. Incidence of clinical endpoints will be estimated from existing literature, with such estimates for adverse birth outcomes being supported by primary data collection. Disability-adjusted life years will be the main outcome, and will be modelled based on clinical endpoints, predicted life expectancy and disability weights.^36^ Intermediate measures include cost per patient screened, diagnosed with an STI and treated. A simple static decision tree model will be used to structure the cost-effectiveness evaluation, which will be from a health system perspective.

Health system costs required to deliver the testing strategy will be collected from both primary and secondary data sources using a bespoke cost extraction tool. Financial and economic costs will be estimated based on study financial records, staff interviews, time-and-motion studies and other sources such as national salary scales for the Zimbabwe health service. Cost categories will include start-up costs such as training costs, capital costs including buildings and storage and equipment, and recurrent costs, including personnel, consumables, and transport costs. Costs associated with downstream complications of infection will be estimated from the literature. Costs incurred by patients while attending ANC, including transport costs and opportunity costs, will be collected using the interviewer-administered questionnaire. Additional costs associated with the testing strategy, such as a longer visit or to return for treatment, will be recorded.

Individual and combined parameter uncertainty will be investigated using deterministic and probabilistic sensitivity analyses. The cost-effectiveness of the testing strategy compared with syndromic management will be compared against appropriate cost-effectiveness thresholds for Zimbabwe.

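### The planned logistic regression of birth outcomes on STI diagnosis needs at-risk denominators and a way to handle gestation at enrolment; without them the miscarriage odds ratio can be biased in either direction

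*Protocol article*

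**What the plan says.** Protocol article, Statistical analysis, lists "Prevalence of preterm birth, miscarriage and low birth weight" among the other outcome measures. It then gives one sentence on relating them to infection: "Logistic regression will also be used to assess the relationship between STI diagnosis and birth outcomes".

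Study population and recruitment intends enrolment at the first antenatal visit of the pregnancy, admits follow-up attenders if recruitment stays slow, and states no gestational limit. Gestation can be derived, because Study procedures says: "Estimated due date, which will be compared with actual birth date to determine prematurity, will be based on last menstrual period".

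On treatment, the Abstract says "All individuals with STIs will receive treatment". Table 1 schedules treatment for CT, NG, TV and syphilis, and hepatitis B positives have further tests and referral. Treatment may come late or not at all: "Participants who test positive for an STI but are unable to receive same-day treatment will be actively followed up by telephone", and uptake of treatment is itself an outcome.

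On the economic model, Economic evaluation says: "Incidence of clinical endpoints will be estimated from existing literature, with such estimates for adverse birth outcomes being supported by primary data collection".

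**The concern.** Two features of the design affect what this regression can mean.

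- **Entry time.** Women join at whatever gestation they present. Those who join late have already passed through some or all of the period in which a loss or preterm birth could occur. A logistic model that counts every enrolled woman gives late entrants a full place in the denominator and little or no chance of the event. If gestation at enrolment is related to STI status, the model attributes that difference to infection.
- **Contrast.** A diagnosis leads to planned treatment, so the comparison is mostly treated infection against a negative test. Some test-negative women are treated too, since those with discharge receive metronidazole whatever their results. The OR is not the effect of untreated infection.

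A reader could take a biased miscarriage OR as evidence that STIs do, or do not, matter for pregnancy loss. The estimate could also be borrowed for the syndromic-management arm of the economic model, where many infections go untreated.

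**Working it through.** **1. The plan's own figures.** The article gives none for this regression. Its sample size is for composite prevalence and reproduces: n = z²p(1−p)/d² = 1.95996² × 0.30 × 0.70 / 0.03² = 896.3, against 896 stated. At 30% prevalence, 1,000 women give about 300 positive and 700 negative.

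**2. Hand check of the mechanism.** Assume losses spread evenly over weeks 6 to 28. A woman entering at week g still faces (28 − g)/22 of them:
- week 18: 10/22 = 0.455
- week 20: 8/22 = 0.364
- week 22: 6/22 = 0.273
- week 28 or later: 0

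For a rare outcome the OR is close to the ratio of these fractions. With no true effect, positives entering at 22 against negatives at 20 give 6/8 = 0.75. Positives entering at 18 give 10/8 = 1.25.

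**3. Simulation with a spread of entry times.** All inputs are assumptions except 30% prevalence: entry normal with mean 20 weeks in negatives and SD 7 (held to 6–40 weeks), losses in weeks 6–28, no effect of STI. The main run gave these miscarriage ORs:

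| Analysis | Positives enter 2 weeks later | 2 weeks earlier |
|---|---|---|
| All women | about 0.67 | about 1.40 |
| Only women enrolled before the limit | about 0.73 | about 1.33 |
| Stratified by week of enrolment | about 1.0 | about 1.0 |

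A repeat with 10% total loss risk shows how far the size depends on when losses occur:
- Timing density proportional to exp(−0.2(t − 6)): 0.69 and 1.41 in all women, 0.75 and 1.34 after restriction.
- Losses spread evenly: 0.81 and 1.21 in all women, 0.88 and 1.15 after restriction.
- Stratified by week, or with equal entry times: 1.00 to 1.01 in both.

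Across three hazard shapes and differences of 1.4–2.3 weeks later, the range in all women was 0.84 to 0.61. For 1.4–2 weeks earlier it was 1.19 to 1.42.

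**4. Other outcomes.** For preterm birth with entry 1.4–2.3 weeks later, the OR was 0.99–0.98. For a composite in which one third of events are losses, a 4-week difference gave 0.90 (later) or 1.11 (earlier), and 1.00 after stratification. No figure was computed for low birth weight.

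**5. Treatment.** Assume 12% baseline risk and a true untreated OR of 2.0. The odds are 0.12/0.88 = 0.1364; doubled they are 0.2727, a risk of 0.2143 and an excess of 0.0943.
- All treated, half the excess removed: risk 0.1671, OR = (0.1671/0.8329)/0.1364 = 1.47.
- 80% treated, all excess removed: risk 0.1389, OR 1.18.
- All treated, all excess removed: OR 1.00.

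Treatment pulls the OR towards 1, not below it.

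**6. Random error.** The falling-hazard scenarios gave about 6–21 miscarriages per 1,000 women. With 21 split 30:70 (6.3 and 14.7), the standard error of log OR is about √(1/6.3 + 1/14.7) = 0.48. The 95% interval then runs a factor of exp(1.96 × 0.48) = 2.5 either way, so chance would outweigh the bias.

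**The case against.** The strongest reply is that this is one sentence, in a condensed article, about a non-primary observational analysis. Covariates, denominators and handling of entry time are commonly left to an SAP, which is not shown. The text does not say the model is unadjusted, and the data for adjustment are collected. This stands in part: the article cannot be said to have decided to ignore gestation, and the absence of the word multivariable from this sentence proves little. It does not dispose of the point. The article fixes logistic regression with miscarriage as an outcome in a cohort with open-ended entry, and a covariate list would not settle who counts as at risk.

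Three stronger readings are tempting, and the documents do not support them:
- **A spurious protective effect.** This needs STI-positive women to enrol later, which no section says. Earlier entry gives the opposite bias. Even with a true OR of 1.5 and entry 4 weeks later, the composite OR is still 1.34.
- **Every diagnosed infection is treated.** That is the intention. Uptake is measured, untreated women are telephoned, and hepatitis B is referred.
- **The cost-effectiveness result is distorted.** Economic evaluation takes incidence from the literature, uses study birth data only in support, plans sensitivity analyses, and does not name this OR as an input.

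The article also discloses that it makes no formal comparison of birth outcomes with and without the intervention. That is fair disclosure, but it does not say what this regression estimates.

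**Conclusion.** The point holds as a limited one. With open-ended entry, the regression can be biased in either direction if gestation at enrolment differs by STI status. For a 2-week difference and no true effect, the miscarriage OR is about 0.67 to 1.40, and nearer 0.8 to 1.2 if losses are spread evenly over gestation. These sizes rest on assumed entry and loss distributions that the documents do not give. The bias is small for preterm birth and nil if entry does not differ. Separately, the estimate describes diagnosed and mostly treated infection, so it is expected to lie nearer 1 than the effect of untreated infection. Few miscarriages are likely, so the estimate will be imprecise in any case. The composite prevalence, which is the primary outcome, is unaffected.

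**What to change.** Add a few sentences to the analysis text:

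1. Restrict the outcomes to women at risk at enrolment: for miscarriage, those enrolled before the study's gestational limit for that outcome; for preterm birth, those enrolled before 37 weeks. Use the same denominators for the reported prevalences.
2. Analyse time to event with delayed entry at gestation of enrolment, or adjust the logistic model for LMP-derived gestation at enrolment. Restriction alone is not enough (0.73 and 1.33 in the check above).
3. Label the estimate as diagnosed and mostly treated STI versus test-negative.
4. State that it will not serve as the untreated-infection risk in the syndromic-management arm.

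No new data are needed. The cost is fewer women in the miscarriage analysis. With the assumed entry distribution and a 28-week limit, (28 − 20)/7 = 1.14 SD, so about 13% would be excluded. They could not have contributed a miscarriage.
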